### 12.2 Hospitalization

This is defined as the subject being hospitalized overnight, or the subject’s hospital stay being prolonged for at least an additional overnight stay. Preplanned hospital stays or hospital stays for nonmedical social reasons will not be considered as hospitalization. “Twenty-three hour hospitalizations” for observation should be discussed with the medical monitor to determine whether they are appropriate for SAE reporting.

### 12.3 Pregnancy

Female subjects must be surgically sterile (hysterectomy, bilateral oophorectomy, or bilateral tubal ligation) **or** if a female subject is of childbearing potential, she must agree to use a medically acceptable, highly effective method of contraception during the study and for 1 month after the last dose of study drug to be eligible for participation in the study (see Inclusion Criteria, [section 6.2](#); and Contraceptive Measures). All female subjects must have a negative serum pregnancy test at screening and a negative urine pregnancy test at screening day and day 1 to be eligible for the study. A urine pregnancy test will also be performed at the end of the study at the post-treatment follow-up visit.

### ***12.3.1 Pregnancy Follow-up***

Female subjects should be instructed to notify the Investigator if pregnancy is discovered either during or within 4 weeks of completing the last dose. The pregnancy event will be reported in the same reporting time frame as an SAE ([section 12.5](#)) on a specific Pregnancy Report Form, and the status of mother and child will be reported to the sponsor as soon as possible after delivery.

Should a female become pregnant or suspect she is pregnant while participating in this study, or should a male subject's partner become pregnant or suspect she is pregnant while the male is participating in this study, the treating Investigator should be informed immediately. Female subjects will be withdrawn from the study, and all pregnancies will be reported along the same timelines as an SAE.

If a female subject or the female partner of a male subject who has received pirenzepine becomes pregnant, the pregnancy will be recorded. The sponsor and the sponsor's pharmacovigilance group will be informed. The subject will be asked to provide information. The pregnancy will be followed to term and any premature terminations or obstetric complications reported on the outcome of the pregnancy, including premature termination, should the case arise.

Spontaneous miscarriage and congenital abnormalities will be reported as an SAE. All pregnancies involving potential exposure to pirenzepine will be followed to term, and the health status of mother and child will be reported following delivery.

## **12.4 Subject Withdrawal**

If the subject discontinues study treatment due to an AE and withdraws from the study, the reason for the subject withdrawal is to be recorded as due to a specific AE.

## **12.5 Reporting Serious Adverse Events**

**ANY SAE, WHETHER OR NOT RELATED TO THE STUDY TREATMENT, MUST BE REPORTED IMMEDIATELY TO THE SPONSOR'S MEDICAL MONITOR AT THE FOLLOWING NUMBERS:**

PRA Drug Safety Centre  
[contact]  
E-mail: [contact]

WinSanTor or designee will provide details to the Investigator of all serious, unexpected, and related AEs (or other events depending on the specific requirements) from any other ongoing clinical trials that should be reported to IRBs, as appropriate. Confirmation that these serious, unexpected, and related AEs have been submitted to the IRB must be forwarded to WinSanTor or designee within 24 hours of knowledge and also be kept in the Investigator files. The site will report SAEs and AEs to their local IRB in accordance with the reporting guidelines of the IRB/EC.

Fatal or life-threatening, unexpected ADRs occurring in clinical investigations qualify for very rapid reporting. Regulatory agencies should be notified (e.g., by telephone, facsimile transmission, or in writing) as soon as possible but no later than 7 calendar days after first knowledge by the sponsor that a case qualifies, followed by as complete a report as possible within 8 additional calendar days. This report must include an assessment of the importance and implication of the findings, including relevant previous experience with the same or similar medicinal products.

Serious, unexpected reactions (ADRs) that are not fatal or life-threatening must be filed as soon as possible but no later than 15 calendar days after first knowledge by the sponsor that the case meets the minimum criteria for expedited reporting.

## **13 STATISTICS**

No formal power analysis was conducted. However, the population size and duration of the study was based on a similar study designed to observe a positive change in the Norfolk-QOL-DN measurement in 60 subjects with T2DM after 6 months treatment with topiramate and ruboxistaurin ([Boyd et al, 2011](#)).

### **13.1 Methods and Data Analysis**

#### ***13.1.1 Sample Size Justification***

No formal power calculations were performed to estimate appropriate group sizes since this is the first clinical evaluation of WST-057. Cohort size was selected to achieve an appropriate balance between unnecessarily exposing a large number of subjects to a novel therapeutic regimen, having sufficient subjects enrolled to interpret pharmacodynamic data, and making a reasonable assessment of the dose-related safety of WST-057.

#### ***13.1.2 Study Populations***

Study populations will consist of the safety population, the intent-to-treat (ITT) population, and the per-protocol (PP) population. The safety population will consist of all subjects receiving at least 1 dose of study drug, and will reflect actual treatment received. The ITT population will include all subjects randomized to receive study drug according to randomized treatment who have at least 1 post-baseline measurement. The PP population will include subjects who have at least 80% drug compliance and complete all study visits.

#### ***13.1.3 Demographic/Baseline Information***

Demographic/baseline information will be formally compared between treatment groups and will be summarized within each cohort by treatment group using descriptive statistics. For continuous variables, mean, standard deviation, median, minimum, and maximum will be presented. For categorical variables, N and % will be presented.

### ***13.1.4 Analysis of Safety Data***

The safety end point data will be summarized for the safety population.

The AEs will be coded using the latest version of Medical Dictionary for Regulatory Activities (MedDRA). The incidence of AEs will be summarized by body system and preferred term. A general summary of the AEs and SAEs will be summarized by overall number of AEs, and their intensity and relationship to study drug, per treatment group. The number of AEs leading to withdrawal or SAEs leading to death will also be summarized. The World Health Organization Drug Dictionary Enhanced (WHO-DDE) will be used to classify concomitant medication by therapeutic class and drug name.

The safety laboratory data will be summarized by visit and by treatment group, along with the change from baseline. The values that are below the lower limit or above the upper limit of the reference range will be flagged. Those values or changes in values, which are identified as being clinically significant, will be flagged and summarized separately (with a supporting subject level listing).

The vital signs will also be summarized by visit and by treatment group, along with the change from baseline.

The ECG data will be summarized by standard parameter by time point/visit and by treatment group, along with the change from baseline.

Comparisons will be made between subjects receiving placebo and WST-057 at each dose level. Comparisons will be made among the dose levels, where appropriate. Nonparametric or parametric statistical methods will be used to make treatment group comparisons, where appropriate.

### ***13.1.5 Interim Analysis***

No formal interim analysis is planned for this study. Given the nature of the study design, the safety results will be evaluated as indicated elsewhere in this protocol by appropriately qualified individuals.

### ***13.1.6 Pharmacokinetic Analysis***

Trough blood samples will be collected and analyzed for WST-057 using a validated LC/MS/MS method. Full details of the methodology will be presented in the bioanalytical report, which will be appended to the clinical study report. The data obtained from these analyses will be used to calculate  $C_{min}$ ,  $\lambda_z$ ,  $t_{1/2}$ ,  $CL/F$ ,  $V_z/F$ , and renal clearance ( $CL_r$ ). Further analyses details will be provided in the statistical analysis plan for this study.

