| 
* = It is acceptable to change the schedule of assessments in order to accommodate local and global health concerns and ensure patient safety due to Covid19.
 
a = The ET and EOS visits (week 24) will follow the same procedures.
 
b = Symptom directed physical examination.
 
c = Body weight and BMI calculation only. Height is taken at screening only.
 
d = Blood samples will be collected for serum chemistry and hematology, and urine will be collected for urinalysis (refer to section 7.2.2) at each visit. Subjects will be required to fast for at least 12 hours prior to collection.
 
e = For women of childbearing potential, a serum pregnancy test will be performed at screening and EOS/week 24. A urine pregnancy test will be performed at the Baseline visit.
 
f = Two standard 3-mm skin biopsies will be collected during the Screening visit from the distal leg or calf; approximately 10 cm above the malleolus and 3 cm to the posterior; and from the untreated area on the lateral thigh, approximately 25 cm below the iliac spine, approximately 5 cm below the level of the pubis and 8 cm to the posterior.
 
g = Prophylactic antibiotics may be administered to participants who, in the judgment of the Investigator, are considered to be at high risk for infection of the biopsy site.
 
h = Randomization will be prior to dose administration on day 1.
 
i = Investigational product will be administered by the subject by dispensing material from pump into palms of the hand and then spreading evenly over the calves (mid-calf sock-line), ankles and tops, and bottoms of feet.
 
j = Skin irritation (including dryness, redness, swelling, itching, burning/stinging) at the application site will be assessed using a Dermal Draize Scale prior to dosing on visit days.
 
k = Trough blood samples (1 sample at each specified visit) will be collected for pharmacokinetic analysis.
 
l = Two standard 3-mm skin biopsies will be collected during the EOS visit for early terminations or the week 24 visit. The biopsies will be collected at a distance of no less than 2 cm away and no further away than 3.5 cm from the baseline biopsy location.
 
m = The biopsy sites will be examined at the 26-week visit to monitor healing and remove sutures, if necessary. If the sutures are not suitable for removal, another visit for suture removal will be scheduled.
 
n = The visual analogue score will be collected weekly via a mobile phone application completed by the patient at the same time each week.
 |                |                |            |                |                  |                |                |                |                |                       |                 |

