### 7.3 Pharmacokinetic Evaluations

Trough blood samples will be collected at the time points indicated in the Schedule of Assessments. The concentration of pirenzepine in these samples will be analyzed by a contract bioanalytical laboratory using a validated liquid chromatography coupled to tandem mass spectrometry (LC/MS-MS) method. Full details of the methodology will be presented in the bioanalytical report, which will be appended to the clinical study report. The data obtained from these analyses may be used to calculate the following pharmacokinetic parameters: minimum plasma concentration ( $C_{min}$ ), elimination rate constant ( $\lambda_z$ ), half-life ( $t_{1/2}$ ), apparent clearance ( $CL/F$ ), and apparent volume of distribution ( $V_z/F$ ).

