### 7.5 Total Blood Volume

The total volume of blood obtained from an individual study participant is expected to be approximately 105 mL, including PK samples (14 mL) and clinical laboratory tests (91 mL).

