### 7.6 Pharmacokinetic Sampling

Samples of venous blood will be obtained in dipotassium ethylenediaminetetraacetic acid (K2EDTA) tubes (a minimum of 2 mL per time point required) at the time points indicated in the Schedule of Assessments.

Immediately after collection, the tube will be gently inverted several times to mix the anticoagulant with the blood sample. The plasma fraction will be separated by placing the collection tube into a refrigerated centrifuge (4°C to 8°C) for 10 minutes at approximately  $1500 \times g$ . The plasma fraction will be withdrawn by pipette and divided into 2 polypropylene freezing tubes (designated primary and secondary samples), with each tube receiving approximately equal aliquots. All sample collection and freezing tubes will be clearly labeled in a fashion that identifies the subject, the study period, and the collection time. Labels will be fixed to freezing tubes in a manner that will prevent the label from detaching after freezing. All plasma samples will be processed and placed into a freezer ( $< -20^\circ\text{C}$ ) within 1 hour after collection.

All plasma samples will be stored frozen ( $< -20^\circ\text{C}$ ) until they are shipped to the analytical facility. Prior to shipping, the samples will be packed into thermal insulated containers and packed in sufficient dry ice to assure that they remain frozen for a minimum of 72 hours and protected from breakage during shipment, and will be accompanied by an Excel spreadsheet manifest detailing the contents of each shipment. The bioanalytical facility will be notified of the shipment via e-mail or facsimile. Samples will be shipped by overnight priority courier. The samples will be divided into 2 shipments, each containing 1 aliquot of plasma for each time point. After receipt of verification that the first shipment was received by the analytical facility, the second shipment will be sent. On the day of shipment, the site will e-mail notice to the laboratory and sponsor with the tracking number and a copy of the shipping manifest.

All samples will be shipped to:

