#### **Treatment Period (Day 1 through Week 24)**

- The subject will receive the investigational product and will be trained on how to apply the material on day 1.
- Blood (a single 2 mL sample) will be collected for PK trough levels, at weeks 2, 4, 8, 12, 16, 20, and 24.
- Pharmacodynamic and efficacy evaluations will be performed as indicated in the Schedule of Assessments.
- Blood for clinical laboratory tests will be drawn after an overnight fast (12 hours) at weeks 2, 4, 8, 12, 16, 20, and 24.
- Assessments for AEs and queries for concomitant medication usage will occur throughout the treatment period.

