#### **9.5 Dispensing and Administration of Treatment**

The drug product and corresponding matched placebo will be shipped to the site. All material (labeled metered pumps) will be checked in by the unblinded pharmacist and stored under the appropriate conditions.

Subjects will be randomly allocated in a 1:1:4:4 ratio into placebo 2 mL, placebo 4 mL or one of 2 doses of WST-057 (2.0mL or 4.0 mL). A randomization scheme will be used to program an Interactive Web-Based Response System (IWRS). Eligible subjects will be randomly assigned to a treatment group on Day 1. The randomization number and the study treatment code assigned to a given subject by will be used to select the appropriate bottle of blinded study drug for that subject for the corresponding visit.

Subjects will be instructed on topical administration of 2 mL WST-057 (73 mg pirenzepine free base monohydrate), or 4 mL WST-057 (146 mg pirenzepine free base monohydrate), or 2 mL or 4 mL of placebo based on randomization. The metered pumps are set to deliver 1 mL per pump. Therefore, the investigational product should be administered by the subject by dispensing 2 or 4 pumps of material (placebo or active) into the palm of their hand and spreading evenly over the calves (mid-calf sock line), ankles, and tops and bottoms of feet. After application, subjects will be instructed to allow the material to dry, prior to covering the dosing area with socks or other soft dressing. Therefore, investigational material should be applied during a convenient time of the day, eg, administer drug product in the evening and allow it to dry prior to going to bed. Administration is to be done at approximately the same time every day. The subject will be instructed to store the study drug at refrigerated temperature. The study drug is not to be stored in direct sunlight or left in an automobile. However, the subject may store the IP near their bedside at room temperature in order to support and improve compliance.

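### Section 13.1.6 commits to five PK parameters that one trough plasma sample per visit cannot supply, and Section 7.3 lists a different set

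*Protocol*

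**What the plan says.** Section 13.1.6 (Pharmacokinetic Analysis) states that trough samples will be assayed and continues: "The data obtained from these analyses will be used to calculate" Cmin, λz, t½, CL/F, Vz/F and CLr. It leaves further analysis details to the SAP.

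Section 7.3 (Pharmacokinetic Evaluations) covers the same assays: "The data obtained from these analyses may be used to calculate the following pharmacokinetic parameters". Its list has five entries and omits CLr.

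Sampling is fixed in these places:
- Table 1, footnote k: "Trough blood samples (1 sample at each specified visit) will be collected for pharmacokinetic analysis".
- Section 8.3.1, Treatment Period: "Blood (a single 2 mL sample) will be collected for PK trough levels, at weeks 2, 4, 8, 12, 16, 20, and 24".
- Section 7.6: "Samples of venous blood will be obtained in dipotassium ethylenediaminetetraacetic acid (K2EDTA) tubes", from which plasma is separated. No other PK matrix is described.
- Section 7.5: 14 mL of blood for PK and 91 mL for laboratory tests, about 105 mL in all.
- Table 1: no PK draw at baseline or at the week 26 follow-up.

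Urine is taken for urinalysis, the drug screen and pregnancy testing (Table 1 footnotes d and e; Section 7.2.2).

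On dosing time, Section 9.5 asks for application at a convenient and roughly constant time each day, with this example: "administer drug product in the evening and allow it to dry prior to going to bed". Sections 8.3.1 and 8.4.1 place laboratory blood draws after an overnight fast of about 12 hours.

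**The concern.** The analysis section promises quantities that the sampling schedule does not support. λz and t½ need at least two timed points on the decline after a dose. CL/F needs an area under the curve over the dosing interval, and Vz/F needs both CL/F and λz. CLr needs the amount of drug excreted in urine over a timed period. With one plasma value per dosing interval and no urine assayed for drug, none of these can be formed. The study report would have to depart from a firm commitment or list the parameters as not calculable.

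The two PK sections also disagree on whether the calculation is mandatory and on which parameters it covers.

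The one remaining parameter, Cmin, depends on the sample being a true end-of-interval trough. The protocol uses the word trough throughout but states no rule linking a subject's chosen dosing hour to the PK draw. These samples are the only systemic exposure data in the trial, and the topical rationale in Section 3.2 rests on limited systemic exposure, so it matters what each value represents.

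**Working it through.** **1. Number of samples.** The visits are weeks 2, 4, 8, 12, 16, 20 and 24, so there are 7. At 1 sample × 2 mL each, 7 × 2 = 14 mL, and 14 + 91 = 105 mL. Both match Section 7.5, so the blood budget holds no additional serial samples.

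**2. What each parameter needs.**

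| Parameter | Definition | Obtainable from one plasma sample per interval? |
|---|---|---|
| Cmin | concentration at end of interval | Yes, if the draw is near 24 h |
| λz | slope of ln C on the terminal decline | No: one point |
| t½ | ln 2 / λz | No |
| CL/F | dose / AUC over the interval | No: no AUC |
| Vz/F | (CL/F) / λz | No |
| CLr | amount in urine / AUC | No: neither term |

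The count is 1 of 6 obtainable and 5 of 6 not.

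**3. Numerical check that troughs do not identify the others.** Take a one-compartment steady-state model with first-order absorption, a 24 h interval and the 73 mg dose. The protocol gives no half-life or absorption rate, so these are assumed: ka = 1/h and a trough of 1 mg/L at every visit. With k = ln 2 / t½,

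V/F = 73 × ka/(ka − k) × [e^(−24k)/(1 − e^(−24k)) − e^(−24ka)/(1 − e^(−24ka))], and CL/F = k × V/F.

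| Assumed t½ | V/F (L) | CL/F (L/h) | Trough (mg/L) |
|---|---|---|---|
| 6 h | 5.5 | 0.64 | 1.0 |
| 12 h | 25.8 | 1.49 | 1.0 |
| 24 h | 75.2 | 2.17 | 1.0 |

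The same trough data fit all three rows equally well.

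**4. Change across visits does not help.** After 14 daily doses (nominal week 2), the fraction of steady state is 1 − 2^(−336/t½). This gives 99.99% for t½ = 24 h, 99.2% for 48 h, 96.1% for 72 h and 75% for 168 h. Unless the half-life is very long, every visit is already at or close to plateau, and there is no first-dose sample for comparison.

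**5. Secondary point: time after dose at the draw.** Clock times are assumed, because the protocol gives none: application 19:00 to 23:00 and draw 07:00 to 11:00. The shortest gap is 1 + 7 = 8 h and the longest is 5 + 11 = 16 h, with a midpoint of 12 h, against 24 h for a true trough.

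To illustrate only, under mono-exponential decline C(12 h)/C(24 h) = 2^(12/t½). This is 4.0, 2.0, 1.4 or 1.2 for an assumed t½ of 6, 12, 24 or 48 h. Slower absorption pulls the ratio towards 1. In the model of step 3 with ka = 0.2/h, it falls from 2.0 to about 1.8 at t½ = 12 h, and from 1.4 to about 1.3 at 24 h.

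**The case against.** **The SAP may deal with it.** Section 13.1.6 defers analysis detail to the SAP. That covers methods, but an SAP cannot supply samples or urine that were never collected. The commitment to the parameters is made in the protocol itself.

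**A population model could give CL/F.** In theory, yes, if dose-to-sample times vary and are recorded. The protocol describes no such model, and it still would not yield CLr. This is why the point is limited to conventional methods for the other four parameters. A reader might also infer that any half-life reported would be made by joining troughs taken weeks apart. The protocol describes no such method, so that is speculation.

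**Urine is collected.** True, so the protocol should not be read as having no urine collection. What is absent is timed urine assayed for drug.

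**The dosing-hour point is inference.** This largely stands. A reader might conclude that evening users are sampled 12 h after dosing. However, evening is only an example in Section 9.5, visit clock times are not given, and the pre-dose rule in Section 7.2.2 is written for laboratory samples. Sites may have instructions that are not shown. Timing data may also exist: Section 7.6 puts collection time on the tubes, and Section 14.8 requires drug administration to be documented in source. What remains is that the protocol states no rule tying dosing time to the PK draw.

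**Little depends on PK.** Correct. No objective (Sections 4.1 to 4.3), endpoint (4.4, 4.5), stopping criterion (5.2) or sample-size argument (13, 13.1.1) uses a PK parameter. The protocol specifies no 2 mL versus 4 mL exposure comparison. Dosing hour is not tied to randomized arm, so the expected effect is added variability rather than a biased dose contrast.

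**Conclusion.** The point holds. Five of the six parameters in Section 13.1.6 cannot be calculated by conventional methods from the sampling described, and CLr cannot be obtained by any method without drug measured in urine. This follows from the definitions and from the protocol's own sample count and needs no outside figure. Sections 7.3 and 13.1.6 also contradict each other on obligation and on CLr.

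The dosing-hour point is secondary. It rests on assumed clock times (8 to 16 h after dose), and the fold factors rest on assumed half-lives and a simple decline. They show what could happen and do not demonstrate a bias.

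The grade is should-fix. A reader might take the point as a threat to the trial's main conclusions, but the documents do not support that: the safety objective and the IENFD and Norfolk-QOL-DN objectives do not depend on these parameters.

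**What to change.** 1. In Sections 7.3 and 13.1.6, delete λz, t½, CL/F, Vz/F and CLr, so that the two sections agree with each other and with Table 1.
2. State instead that trough concentration will be summarized by visit and dose level. A 4 mL to 2 mL geometric mean ratio is optional. An accumulation analysis is not worth adding, because sampling starts at week 2.
3. Capture the date and time of the last application at each PK visit, if it is not already recorded. Report concentrations with time since last dose, and label as Cmin only samples near the end of the dosing interval.
4. Reconcile the dosing-time text in Section 9.5 with the trough description in the PK sections. How that is done is for the sponsor to decide.

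The cost is wording in two sections and at most one eCRF time field. The protocol promises fewer PK parameters, but it gives up none that its sampling could have delivered by conventional methods.
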